### Outcome measures

#### Primary outcome

The number of days alive without unplanned hospitalisation within 1 year of follow-up is derived from the number of unplanned hospital days as collected in the HF registry (table 1).

**Table 1 T1:** Operationalisation of exposure variable and study outcomes

Variable	Source	Time of collection	Operationalisation
Exposure			
Telemedicine	HF registry, telemedicine-generated data	T0, T1*, T2	Whether a patient receives telemedicine. Five categories: (1) no telemonitoring†; (2) telemonitoring by telephone; (3) telemonitoring, non-invasive based on traditional parameters (eg, blood pressure, ECG); (4) telemonitoring using ICD based on HF parameters; and (5) telemonitoring, invasive using sensors in the bloodstream or heart.
Primary outcome			
Number of days spent alive without unplanned hospitalisations within 1 year of follow-up	HF registry	T1*, T2	Number of days directly related to unplanned cardiac hospital admission due to HF. Number of admission days will be summed up over a period between follow-up moments and subtracted from 365 days.
Secondary outcomes			
Costs	Derived from HF registry, external data source, EHR, interviews	T0, T1*, T2	Costs estimated from patient, disease and treatment characteristics. Information taken into account includes medication use, whether the patient underwent cardiac interventions (eg, pacemaker implantation, percutaneous coronary intervention), use of telemedicine, hospital admission days, visits to the outpatient clinic, visits to the emergency room, admission days at an intensive care unit and visits to the GP related to HF.
All-cause mortality	HF registry, external data source	T1*, T2	Mortality status, determined after verification at the Personal Records Database (in Dutch: Basisregistratie Personen). Mortality is independent of HF (all-cause).
Functional status	HF registry	T0, T1*, T2	NYHA classification: a functional classification of patients based on severity of symptoms and physical activity, with specific attention to fatigue, palpitation and dyspnoea. Scores are linked to one of four NYHA classes: class I: no limitation; class II: slight limitation; class III: marked limitation; and class IV: unable to carry on any physical activity without discomfort.^1^

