The primary outcome model is a linear mixed model with a random intercept for the participating centre and is specified as follows. The outcome is measured in days, and because the final measurement may be less or more than 365 days after baseline, we rescale the number of days of unplanned hospitalisation to the number of days under follow-up to 365 days. The outcome is computed by subtracting the days of unplanned hospitalisation or death from 365. The earlier described confounding variables are added to the primary outcome model to adjust for confounding. Continuous covariates are modelled using splines. Multicollinearity between confounding variables and the telemedicine status is evaluated. The coefficient for telemedicine in the primary outcome model represents the average treatment effect of offering any telemedicine within 3 months after HF diagnosis compared with not offering telemedicine on days with unplanned HF-related hospitalisation during a year in the population of patients with newly diagnosed HF. Robust SEs are estimated to compute CIs.

For the secondary outcome functional status, a similar approach is taken to estimate the average treatment effect of offering any telemedicine within 3 months after HF diagnosis compared with not offering telemedicine on functional status after 1 year in the population of patients with newly diagnosed HF. For this analysis, the outcome model is a multinomial regression model, and baseline functional status is added as a covariate. The risk difference relative to the reference outcome category is assessed using the predicted outcomes of the primary outcome model offering of telemedicine versus not offering, to obtain the marginal risk difference.^38–40^ Similarly, for the secondary outcomes health status and hrQoL, the outcome model is a probit regression model, with baseline measurements added as a covariate. Healthcare utilisation will be assessed using a Poisson regression model, and all-cause mortality will be assessed using binary logistic regression.

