##### Research question 2: effectiveness of different telemedicine components

Research question 2 investigates the effectiveness of the different forms of telemedicine intervention. We assess this question by performing three separate analyses in which intervention aspects are contrasted in the subset of participants that received telemedicine. The presence or absence of a telemedicine component is determined at a hospital level. The components of telemedicine that are contrasted are presence versus absence of a service centre, presence versus absence of an educational module, and high-intensity versus low-intensity protocol (table 2).

The population of interest is patients with newly diagnosed HF (maximum 3 months prior to baseline) who received telemedicine. Offering of telemedicine is measured at 6 months after baseline.

In addition to the set of confounding variables at the patient level used in the analysis above, confounding variables at the hospital level are considered because indication for telemedicine is expected to differ across hospitals. Confounding variables include academic or non-academic hospital, presence of a specialised heart centre, presence of an outpatient ward, size of outpatient ward (number of patients/year), staffing of the HF outpatient clinic and full-time equivalent of outpatient-ward staff.

For each of the three contrasts, the primary outcome model is fitted to estimate the average treatment effect of a component relative to the corresponding reference component on days of unplanned hospitalisation during 1 year in the population of patients with newly diagnosed HF that initiated telemedicine.

The secondary outcomes functional status, health status and hrQoL are assessed using similar approaches but using multinomial, probit and probit regression model, respectively. Healthcare utilisation and all-cause mortality will be assessed using Poisson regression model and binary logistic regression, respectively.

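### The primary outcome's definitions conflict on whether death counts, and the rescaling of hospital days makes no exception for patients who die

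*Protocol article*

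**What the plan says.** The Primary outcome section and its Table 1 label the outcome "Number of days spent alive without unplanned hospitalisations within 1 year of follow-up". The running text says that it "is derived from the number of unplanned hospital days as collected in the HF registry". The operationalisation column of Table 1 gives the days to be counted as "Number of days directly related to unplanned cardiac hospital admission due to HF" and the computation as "Number of admission days will be summed up over a period between follow-up moments and subtracted from 365 days". Death appears in the label and not in the computation.

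The section Preparation of the statistical model gives a different rule: "The outcome is computed by subtracting the days of unplanned hospitalisation or death from 365". Before that step, "we rescale the number of days of unplanned hospitalisation to the number of days under follow-up to 365 days", and the reason given is "because the final measurement may be less or more than 365 days after baseline". The article does not say whether this rescaling applies to patients who die, or whether their follow-up ends at death.

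The same section then interprets the telemedicine coefficient as an effect on days with unplanned HF-related hospitalisation. Research question 2 does likewise for the component contrasts: "on days of unplanned hospitalisation during 1 year". Neither description mentions death.

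**The concern.** Analysts working from Table 1 and from the model section would build different variables. Under Table 1 as written, a patient who dies without an HF admission receives the best possible score. A patient who dies also accrues no further hospital days, so an exposure that raised mortality could look beneficial. Under the model section the same death costs every day from death to day 365.

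The coefficient descriptions add a third version. An effect on hospitalisation days leaves out death and has the opposite sign to an effect on days alive and out of hospital.

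The rescaling raises a separate question. If hospital days are scaled up to a full year for someone who died part-way through, and the days after death are then also subtracted, the time after death is charged twice.

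This variable carries the main effect, the subgroup analyses of research question 1 and the component contrasts of research question 2, so the ambiguity reaches all of them.

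**Working it through.** **The plan's own figure.** The sample size section assumes a difference of 6.4 days with SD 21.1, a 5% type I error, 80% power and 20% dropout. Taking a two-sided test and 1:1 allocation (neither is stated):

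- Per group: 2 × (1.960 + 0.842)² × 21.1² / 6.4² ≈ 170.6, so 171; in total 342.
- With dropout: 342 / 0.80 = 427.5, so 428. The t-based version gives 172 per group, and 344 / 0.80 = 430.

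Both are close to the stated 432, so the figure reproduces and this point does not disturb it. The 6.4 days and the SD of 21.1 serve below as yardsticks.

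**Death in the definition.** Let t be the day of death and H the unplanned HF hospital days before it.

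- Table 1: Y = 365 − H.
- Model section without rescaling: Y = 365 − H − (365 − t) = t − H.

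For death on day 200 with H = 0, Table 1 gives 365 and the model section gives 200. The gap is 165 days for one patient, or 165 / 21.1 ≈ 7.8 of the assumed SDs. This patient lived past 6 months, so the example does not depend on how early deaths are classified for exposure.

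**What a mortality difference is worth.** The article gives no mortality rate or timing, so both lines assume uniform timing of deaths.

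- Over the whole year: mean days lost per death = 365 / 2 = 182.5. One percentage point is worth 0.01 × 182.5 = 1.825 days, and 6.4 / 1.825 ≈ 3.5 points.
- Only over the second half-year, because telemedicine status is set at the 6-month measurement: mean days lost = 182.5 / 2 = 91.25. One point is worth 0.9125 days, and 6.4 / 0.9125 ≈ 7.0 points.

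Table 1's rule gives zero days for the death component in both cases.

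**Rescaling applied literally to a death.** Suppose follow-up ends at t, hospital days are multiplied by 365/t, and the days after death are then subtracted in full:

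Y = 365 − 365H/t − (365 − t) = t − 365H/t, instead of t − H.

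| t | H | Literal rescaling | No rescaling (t − H) | Table 1 (365 − H) |
|---|---|---|---|---|
| 30 | 2 | 5.7 | 28 | 363 |
| 60 | 20 | −61.7 | 40 | 345 |
| 180 | 20 | 139.4 | 160 | 345 |
| 300 | 30 | 263.5 | 270 | 335 |

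The t and H values are illustrative. For every death before day 365 with H > 0, the literal value falls below t − H. It is negative only if H > t²/365: more than 2.5 hospital days for death on day 30, 9.9 on day 60, 22.2 on day 90, 88.8 on day 180 and 246.6 on day 300.

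**The case against.** The outcome is named as days alive in the abstract, the objectives, Table 1's own label, the model section and the sample size section. The explicit rule for the model does subtract death. On this view Table 1 merely lists the registry component, the coefficient wording is shorthand, and the intention is clear. That may well be the intention. But the Table 1 entry is presented as the operationalisation and describes a complete computation, and the running text agrees with it. This is a conflict between printed statements, not a detail left to an analysis plan.

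A reader might infer that the rescaling rule generally gives negative day counts for patients who die. The article does not support that. Its stated reason for rescaling is the timing of the final measurement, and it nowhere says that hospital days of deceased patients are scaled up. If they are not, the value is t − H and cannot be negative. Even on the literal reading, a negative value needs H > t²/365. Deaths before 6 months may also lack the exposure measurement that defines telemedicine status. Table 1 lists baseline exposure as well and start dates are to be collected, so such patients may still enter, but the article leaves this open. For deaths around day 180 a negative value would need about 89 hospital days. What stands is that no exception is stated, and that the literal rule double-counts.

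Bounds and minimum follow-up for survivors can be left to an analysis plan and are not part of this point.

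**Conclusion.** The conflict on death is established from the text alone and needs no assumption: Table 1 omits death, the model section counts it, and the coefficient descriptions omit it again with the sign reversed. Single patients can differ by 165 days or more, against an assumed effect of 6.4 days. Uniform timing of deaths, which is an assumption, puts the mortality difference that matches that effect at about 3.5 points over the full year, or about 7 points if only deaths after 6 months are analysed. Actual mortality and its timing are not given, so it cannot be said that the result would change, only that it could.

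The rescaling part is conditional. Read literally, the rule double-counts time after death whenever there were hospital days. Negative values would be confined mainly to early deaths with substantial hospital time, and the authors may not intend the rule for deaths at all. The definition should be settled before the outcome is derived.

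**What to change.** Use one formula in the Primary outcome text, Table 1, the model section and Research question 2: days alive up to day 365 minus unplanned HF hospital days in that period, that is, min(t, 365) − H. State that hospital days are not rescaled for patients who die, so that rescaling applies only to survivors whose final measurement is not at day 365. Describe the coefficient everywhere as the difference in days alive without unplanned HF hospitalisation, with positive values meaning benefit.

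The worked example of death on day 180 after 20 hospital days then scores 160 under every section, and no death can score below zero.

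The cost is wording and derivation code. The study already plans to report time until death, so the death component should need no new variable. Table 1 refers only to verified mortality status, so it would help to name the source of the death date.

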##### Preparation of the statistical model

As a first step, we describe how the overall effect of offering any type of telemedicine versus not offering telemedicine will be estimated. This analysis will subsequently be used for a comparison of telemedicine effects on days alive without unplanned HF-related hospitalisation during 1 year across subgroups.

The cohort is restricted to individuals with newly diagnosed HF, that is, at most 3 months prior to baseline. The exposure contrast is defined as offering any type of telemedicine after first presentation with HF at the hospital outpatient clinic versus patients not offered telemedicine. The telemedicine status for the entire follow-up is defined by 6 months after baseline measurement of telemedicine, used as an observational analogue of an ‘intention to treat’ analysis in which the stopping of telemedicine is disregarded.

Because telemedicine administration is dependent on patient characteristics, confounding by indication will be accounted for. Based on clinical consensus, the following patient-level confounding variables measured at baseline will be adjusted for: age, sex, SES, BMI, NYHA, LVEF, aetiology of HF, systolic blood pressure, diastolic blood pressure, heart rhythm, heart rate, chronic respiratory disorders, OSAS, stroke, extra cardiac arterial vascular pathology, DM, hypertension, anaemia, CKD, malignancy, heart rhythm disorders, depression and thyroid disease (see table 3 and online supplemental material 1).

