##### Research question 1: effectiveness of telemedicine in patient subgroups

Research question 1 investigates the effectiveness of telemedicine across subgroups of patients with HF. Patient-related subgroups were identified by a systematic literature review of randomised controlled trials (RCTs) of telemedicine: age, severity of HF (NYHA class at baseline), sex, SES, presence of depression, atrial fibrillation and type of HF (HF with preserved ejection fraction (HFpEF), HF with midrange ejection fraction (HFmrEF), HF with reduced ejection fraction (HFrEF)) (table 3).^20–24 41–49^ Stratified analyses of the primary outcome model are performed to estimate the above-defined average treatment effect in each of the subgroups. Heterogeneity in telemedicine effect across age is assessed on a continuous scale, where an interaction between age and telemedicine status is added to the primary outcome model, and the expected number of days out of hospital across age ranges from 50 to 90 years is predicted from this model under telemedicine offered versus not offered.

In an additional analysis, heterogeneity across time since diagnosis is explored for the entire cohort, without restricting to patients with a maximum of 3 months since HF diagnosis at baseline (diagnosed ≤3 months before baseline compared with >3 months before baseline).

The secondary outcomes functional status, health status and hrQoL are assessed using similar approaches but using multinomial, probit and probit regression model, respectively. Healthcare utilisation will be assessed using a Poisson regression model, and all-cause mortality will be assessed using binary logistic regression.

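### The one stated diagnostic, collinearity of the confounders with telemedicine, does not reliably detect poor overlap, yet predictions under both exposures are fixed for ages 50 to 90 whatever the data support

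*Protocol article*

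**What the plan says.** All references are to the Statistical analysis part of the protocol article.

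- **Preparation of the statistical model** expects selection: "Because telemedicine administration is dependent on patient characteristics, confounding by indication will be accounted for". It lists 23 patient-level confounders, including age, NYHA class, LVEF, SES and depression: "Based on clinical consensus, the following patient-level confounding variables measured at baseline will be adjusted for".
- Adjustment is by outcome regression in a linear mixed model: "The earlier described confounding variables are added to the primary outcome model to adjust for confounding". On functional form: "Continuous covariates are modelled using splines". The telemedicine coefficient is read as an average treatment effect "in the population of patients with newly diagnosed HF. Robust SEs are estimated to compute CIs".
- The only model diagnostic is: "Multicollinearity between confounding variables and the telemedicine status is evaluated". No measure, threshold or resulting action is named.
- **Research question 1** uses the same model by subgroup: "Stratified analyses of the primary outcome model are performed to estimate the above-defined average treatment effect in each of the subgroups". Age is handled on a continuous scale through an interaction with telemedicine status, whose form is not given. From that model, "the expected number of days out of hospital across age ranges from 50 to 90 years is predicted from this model", under telemedicine offered and not offered. The range is not tied to the ages at which both groups are observed.

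**The concern.** Association between confounders and telemedicine is what confounding by indication consists of, so a collinearity check will flag something the plan already expects. The standard error of the telemedicine coefficient already carries the cost of that association.

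The less visible threat is a region of the covariate space, such as the oldest patients, where one exposure group is almost or wholly absent. There the model supplies the missing half of the comparison from elsewhere. A global collinearity measure averages over all patients and can stay low when this happens.

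Research question 1 asks in whom telemedicine works. At the ends of a curve fixed from 50 to 90 years, the answer could come from the form of the interaction term and not from patients, and the confidence interval would not necessarily show it.

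**Working it through.** **The plan's own figures.** The article gives none for collinearity, overlap or uptake, so there is nothing on this point to reproduce. Two inputs come from the Sample size calculation: N = 432 × 12 = 5184 and SD 21.1 days. That calculation is not disputed here.

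**Assumptions (not in the documents).** Age is normal with mean 73 and SD 11. Uptake by age takes one of the four patterns below.

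**Step 1: VIF against overlap.** VIF = 1/(1 − R²), where R² comes from regressing telemedicine status on age. Age enters linearly or as a 4-df spline; the spline is closer to the plan. Simulated averages:

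| Assumed uptake | VIF linear | VIF spline | Users / non-users aged ≥80 |
|---|---|---|---|
| 20% below 80, none from 80 | 1.04 | 1.05 | 0 / about 1360 |
| 50% below 80, none from 80 | 1.13 | 1.17 | 0 / about 1359 |
| Smooth steep gradient, 1/(1+exp((age−70)/8)) | 1.34 | 1.36 | about 172 / 1187 |
| All below 73, none from 73 | 2.8 | 5.7 | 0 / about 1360 |

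In the first three rows the order is the wrong way round: VIF is lower where overlap is absent from 80 than where it is kept. Only near-complete separation raises it clearly.

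**Step 2: closed-form check.** Let P be the share under 80: P = Φ((80−73)/11) = 0.738, so 5184 × 0.262 ≈ 1360 patients are 80 or over. With uptake p below 80 and zero above, the largest R² that any function of age can reach is p²P(1−P) / [pP(1−pP)].

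- p = 0.5: 0.0484 / 0.2328 = 0.208, so VIF is at most 1/(1−0.208) = 1.26.
- p = 0.2: 0.00774 / 0.1258 = 0.062, so VIF is at most 1/(1−0.062) = 1.07.

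However flexibly age is modelled, the age part of the VIF stays close to 1 with no user aged 80 or over. The other 22 confounders would add to the VIF, but for reasons unrelated to this gap.

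**Step 3: consequence for the age curve.** Take 50% uptake below 80 and none from 80. Let the true effect be 6.4 days up to 75, fall to 0 at 85 and reach −3.2 at 90, with residual SD 21.1. Fit a spline for age plus a linear age-by-telemedicine term.

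- Predicted effect at 90: about +4.6 days, SE 1.8.
- Typical 95% interval: 4.6 ± 1.96 × 1.8, about +1.1 to +8.1.
- Truth: −3.2. The error is (4.6 + 3.2)/1.8 ≈ 4.3 standard errors, and coverage is about 1% (0.75% in 400 simulated datasets).

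The sign is wrong and the interval does not show it. This depends on the linear interaction: a spline interaction would give a much wider interval at 90 and reveal much of the problem. The article does not say which is meant.

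**The case against.** The strongest reply is that this is a condensed article. Overlap diagnostics commonly sit in an analysis plan, which is not shown, so their absence here is no fault. That is right, and the point does not rest on it. It rests on two things the article does state: a check unsuited to this threat, and a prediction range fixed without regard to data support.

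Several stronger readings are tempting but are not supported:

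- **Collinearity can never reveal missing overlap.** Too strong. Complete separation raised the VIF to 2.8 to 5.7.
- **Flagged confounders will be dropped, bringing confounding back.** No such step is planned. The set is fixed by clinical consensus, and the article says these variables will be adjusted for. Removal is only a possibility that the sentence leaves open.
- **Every subgroup effect rests on extrapolation.** The model is refitted within strata, so the contrast for one NYHA class is not borrowed from another. A stratum with almost no users would give a very wide interval or no estimate. What remains within strata is extrapolation over the other covariates, which is not quantified here.
- **Overlap does fail in the elderly.** Unknown. Exposure is any type of telemedicine, including telephone and ICD-based monitoring, so near-absence among older patients cannot be presumed.
- **A larger standard error at high ages proves the problem.** It does not. Under an assumed steep gradient (VIF 1.2 to 1.5, with 30 to 71 users against 500 to 545 non-users aged 85 or over), the SE at 90 is 2.2 to 2.6 times that at 70. It is about 1.8 times even with a weak gradient. That is mostly ordinary imprecision, which the interval displays.

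The Abstract also calls the stratified analyses exploratory, which lowers the stakes but does not remove them, because these analyses answer the first research question.

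**Conclusion.** The point holds in a limited form. The stated collinearity check does not reliably detect poor overlap: under the assumed patterns the spline-based VIF is 1.05 to 1.17 with no users aged 80 or over, below the 1.36 seen when users remain. The age curve from 50 to 90 can therefore include predictions that come from the model alone. In one deliberately unfavourable case the estimate at 90 had the wrong sign and an interval that excluded the truth. Covariate adjustment within strata is exposed to a lesser extent.

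The sizes rest on an assumed age distribution, assumed uptake by age, an assumed reversal of effect and a linear interaction. They show what the check can miss, not what the registry will contain. The change is worth making because it is cheap and the affected predictions bear directly on research question 1.

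**What to change.** 1. Replace or supplement the collinearity sentence with a comparison of the estimated probability of telemedicine, or of the covariate distributions, between users and non-users. Do this overall and in each research question 1 subgroup.
2. Show the numbers of users and non-users along the age curve. Limit the curve to ages where both are present in reasonable number, or mark the sparse range as extrapolation. Treat strata in the same way.
3. If the collinearity check is kept, say what it is for, and state that the consensus confounder set is retained whatever it shows.

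The cost is a little extra analysis on data already being collected. The downside is that some ages or strata may have to be reported as not supported by the data.
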